### Study groups

The podiatry service will operate from the La Trobe University Health Sciences Clinic in Melbourne, Australia. Given this is a pragmatic trial, participant needs will be triaged during the baseline assessment, which will determine the types of interventions provided by the podiatry service. Based on previous research [20], it is anticipated that treatment will involve broad categories of:dermatological care (nail and callus care, education);musculoskeletal care (managing pain, deformity, and improve function using: (i) medication in conjunction with medical team, (ii) strengthening exercise and stretches, (iv) foot orthoses, (v) in-shoe padding, (vi) toe splints, and (vii) education);neurovascular care (assessment, education, management where appropriate, and referral if needed);foot ulcer management (pressure offloading, wound care and dressing, and referral where appropriate);footwear education and modification.

Treatment will be provided by a podiatrist with over 10 years of experience in clinical practice, who is endorsed to prescribe scheduled medicines, has undertaken further training in rheumatological conditions, and plays an active role in the Australian Rheumatology Association. For participants who require foot orthoses, Formthotics™ (Foot Science International, Christchurch, New Zealand) full length prefabricated foot orthoses will be provided. These are manufactured from a dual-density polyethylene closed cell foam that has a firm-density bottom layer (Shore-A durometer 50), and a soft-density top layer (Shore-A durometer 25). Participants will be provided the foot orthoses in accordance with the manufacturer’s instructions by selecting an appropriate size, heating the foot orthoses using a specifically designed machine from Foot Science International, placing them within the participants footwear, and asking participants to stand to allow the foot orthoses to mould to the contour of the foot. Adjustments to the foot orthoses will be made to ensure the participants agree they are comfortable. Participants who require footwear will be provided with a $250 discount from the cost of new footwear. The footwear will be agreed with the podiatrist and participants will be required to attend pre-arranged footwear suppliers to receive the discount. Advice provided to participants about footwear is included in Online Resource 1. All other treatment, such as skin or nail care, exercises, or other aids, will be provided in line with standard podiatry practice in Australia.

The control group will receive usual care plus a self-management package based on advice from Creaky Joints Australia (29 Tips from Podiatrists for Managing Arthritis Pain in Your Feet), which provides a range of education including regular self-inspection of feet, advice about exercising to reduce foot/ankle discomfort, selecting appropriate footwear, and the use of supportive aids such as foot orthoses, ice packs, salt baths etc. For usual care, participants will be advised they can seek any treatment they prefer over the 12-week duration of the trial and their progress will be monitored. At the conclusion of the trial, participants randomised to the control group will be invited to attend a debriefing session and will be offered the same treatment as the intervention group if the intervention is found to be effective.

### Patient and public involvement

Recognising the importance of designing patient-centred research, we included a consumer as a coauthor (KL) during the initial design of the trial and securing grant funding. To further inform the trial design, we conducted four semi-structured interviews with people who have a rheumatological condition and foot-specific complaints. These interviews aimed to gather detailed feedback on various aspects of the trial, including the acceptability of the intervention, the feasibility of the proposed procedures, potential barriers to participation, and what outcomes are important. The interviews were conducted prior to the approval of the ethics application.

Participants will be recruited from outpatient rheumatology clinics at Austin Health in Melbourne, Australia. Rheumatologists will be informed about the trial and asked to recommend that their patients consider participating if they have foot-specific symptoms. Therefore, rheumatologists will initially approach participants about participating in the study and recommend that potential participants contact the researchers via a website. To be eligible for inclusion, participants must:be adults over 18 years of age;have a diagnosis of a rheumatological condition from a rheumatologist;have foot-specific symptoms rated 3/10 or greater on a numerical rating scale (e.g. pain, stiffness, dermatological complaints); andhave experienced symptoms for at least four weeks.

Participants will be excluded if they:are unable to understand the English language in verbal or written form;have regularly attended a podiatry service for management of their rheumatological foot problem in the past 3 months;have an active bacterial infection of the foot; andexperience foot symptoms that are not related to the rheumatological condition.

The recommended sample size for feasibility studies is 12 people per group [21], however to allow for a 20% drop-out rate, we will recruit 15 participants per group. This is similar to the median sample size of 30 for pilot trials documented in the United Kingdom Clinical Research Network database [22]. Given the low-risk nature of the interventions, we are not specifying interim analyses or guidelines for stopping the trial.

### Main outcome variable: feasibility

Given this is a pragmatic trial, the framework developed by Chan et al. [23] will be used to determine feasibility. According to this framework, 10 important domains of uncertainty should be addressed in a pragmatic feasibility trial. These domains are outlined in Table 1 along with criteria that will determine whether a larger trial is feasible. In addition to the feasibility outcomes, data will be collected on participant characteristics, adherence to interventions, adverse effects and acceptability and credibility of the interventions. These outcomes are outlined in detail in Online Resource 2.

**Table 1 Tab1:** Domains and criteria used to evaluate trial feasibility

Domains of uncertainty	Criteria
1. Intervention development	No significant barriers to implementation of interventions are identified
2. Research ethics	No concerns are identified by the ethics committee
3. Participant identification and eligibility	There is a conversion rate of at least 75% (i.e. at least 75% of people screened are enrolled in the trial)
4. Recruitment	At least 5 participants are recruited per month
5. Setting	At least 60% of participants are recruited from rheumatology departments located in hospitals in northern Melbourne, Australia
6. Organisation	Resources required for the trial do not exceed the budget
7. Flexibility of delivery	There are minimal deviations from how interventions are delivered in clinical practice
8. Flexibility of adherence	The median self-reported adherence to the intervention is at least 3 ‘Sometimes’ on a Likert scale from 1, ‘Strongly disagree’ to 5 ‘Strongly agree’
9. Follow-up	Questionnaire completion rates at weeks 6 and 12 are at least 75%
10. Primary outcome	Semi-structured consumer interviews identify goal attainment as the most important outcome

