## Abstract

People with rheumatological conditions often experience debilitating foot-related symptoms requiring expert multidisciplinary care. However, in Australia there is a glaring gap in the provision of universally accessible, publicly-funded podiatry services. This study aims to assess the feasibility of a randomised trial evaluating a publicly-funded podiatry service for people with foot-specific symptoms related to rheumatological conditions. A pragmatic, participant-blind, parallel-group, randomised feasibility trial will compare effectiveness of a podiatry service with usual care. Consumer interviews will inform the design of the feasibility trial. Thirty adults with a rheumatological condition and foot specific symptoms will be recruited from an outpatient rheumatology clinic and randomised to receive access to a podiatry service or a control group who will receive usual care. Outcome measures will be obtained at baseline, week 6 and week 12. Feasibility will be evaluated using a framework that includes 10 important domains of uncertainty in pragmatic feasibility trials. Secondary outcomes (such as Goal Attainment Scaling) will also be collected and effect sizes of between group differences calculated to signal efficacy. The study will explore the feasibility of conducting a fully powered randomised trial of the effectiveness of a podiatry service for people with a rheumatological condition and foot-specific symptoms. In addition, the trial will determine the feasibility of Goal Attainment Scaling as a primary outcome measure for this population.

Trial registration.

The trial is registered with the Australian and New Zealand Clinical Trial Registry (ANZCTRN12625001000493 on the 9th of September 2025).

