## Methods

This will be a pragmatic, participant-blind, parallel-group, randomised feasibility trial comparing access to a podiatry service with usual care. The trial is registered with the Australian and New Zealand Clinical Trial Registry (ANZCTRN12625001000493) and has been developed in accordance with the SPIRIT 2025 statement [17], the CONSORT 2010 statement extension to randomised pilot and feasibility trials [18], and the TIDieR checklist for reporting of interventions [19]. Ethics approval has been obtained from the La Trobe University Human Ethics Committee (Approval number HEC25095 on the 20th of May 2025) and written informed consent will be obtained from all participants during the baseline assessment.

The randomisation module in REDCap (Research Electronic Data Capture, Vanderbilt University, USA) will be used to randomise participants. Participants will be allocated on a 1 to 1 ratio with blocking in groups of 4 and 6, and stratification based on sex at birth to ensure a balance of participant sex between the groups. Allocation will be concealed from all researchers until after eligibility screening. Participants will be randomised to their intervention after completing consent at the baseline assessment.

Given this is a feasibility trial, only participants will be blind to their allocation. Both groups will be blind to group allocation through limited disclosure. All participants will be informed that two different types of treatment are being compared, however only the intervention group will be informed about the additional access to podiatry treatment.

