One objective for this feasibility trial is to evaluate the feasibility of using patient-centred goal attainment outcome measures (Goal Attainment Scaling). Goal Attainment Scaling is a structured method used to set and measure the achievement of patient-centred goals. The overall effectiveness of the intervention is determined by aggregating individual goal scores into a single t-score. Goal Attainment Scaling has several benefits, such as allowing patient-centred outcomes, greater sensitivity to change compared to standardised measures, and flexibility in settings with heterogenous participants. However, there are some challenges when implementing Goal Attainment Scaling in a randomised trial, such as ensuring consistent goal-setting across different practitioners, managing patient expectations, and dealing with the subjective nature of goal assessment [26].

This protocol outlines the methods for a participant-blinded, parallel-group randomised feasibility trial to compare the addition of a podiatry service to usual care for people with a rheumatological condition and foot specific symptoms. In addition to determining whether a larger randomised trial is feasible, this trial will also evaluate whether it is feasible to use Goal Attainment Scaling as a primary outcome measure and provide data to determine a suitable sample size.

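### The Table 1 criterion for the primary outcome (domain 10) does not test whether Goal Attainment Scaling is feasible: it rests on consumer interviews, and the only ones described took place before ethics approval

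*Protocol article*

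**What the plan says.** The Abstract and the Discussion both make the feasibility of GAS as a primary outcome a question for the trial. The Discussion puts it as "this trial will also evaluate whether it is feasible to use Goal Attainment Scaling as a primary outcome measure".

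The section on the main outcome variable says that the Table 1 criteria decide whether a larger trial is feasible. For domain 10 the whole criterion is "Semi-structured consumer interviews identify goal attainment as the most important outcome".

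On the interviews, the section on patient and public involvement reports that "we conducted four semi-structured interviews with people who have a rheumatological condition and foot-specific complaints", and adds: "The interviews were conducted prior to the approval of the ethics application". The Abstract uses the future tense but gives them the same role: "Consumer interviews will inform the design of the feasibility trial". The Procedures section describes no interviews during the trial.

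GAS is measured at baseline and week 12 (Table 2). Goals are kept on paper, and the Chief Investigator enters the change in REDCap at the in-person week-12 visit (Procedures). Domain 9 asks for at least 75% questionnaire completion at weeks 6 and 12 and does not mention GAS.

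Two other criteria matter here. Domain 2 asks that the ethics committee identify no concerns, and the Methods state: "Ethics approval has been obtained from the La Trobe University Human Ethics Committee". Domain 5 reads: "At least 60% of participants are recruited from rheumatology departments located in hospitals in northern Melbourne, Australia". On recruitment the article says: "Participants will be recruited from outpatient rheumatology clinics at Austin Health in Melbourne, Australia".

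**The concern.** A feasibility criterion should be able to come out either way on what the trial observes. Domain 10 takes its answer from a source that precedes randomisation, and it asks a different question from the objective. That patients value reaching their own goals does not show that goals can be set, scaled and scored in this population. The Discussion itself lists the practical difficulties of GAS: keeping goal-setting uniform between clinicians, handling patients' expectations, and the subjectivity of the rating. None has a criterion in Table 1.

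At stake is the choice of primary outcome for the fully powered trial. Under the stated rule, GAS could be carried forward on the interviews alone, even if many participants in this trial had no usable score.

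**Working it through.** **1. The plan's own figure.** 12 per group with 20% drop-out gives 12 / (1 − 0.20) = 15 per group, 30 in total. This reproduces. The point does not depend on it, but the thresholds below use it.

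**2. Objective against criterion.**

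| | Objective (Abstract, Discussion) | Domain 10 (Table 1) |
|---|---|---|
| Question | Is GAS feasible as primary outcome? | Is goal attainment ranked most important? |
| Source | The trial | Consumer interviews |
| Participants | 30 randomised | 4 interviewed |
| Timing | Baseline to week 12 | Before ethics approval |

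The 30 randomised participants contribute nothing to the domain 10 result.

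**3. Does domain 9 fill the gap?** Only in part. A participant who misses the week-12 visit probably lacks both questionnaires and a GAS score, so domain 9 would register that loss. It does not register a participant who attends, completes the questionnaires and has no scorable goal. Illustration, with assumed counts:
- Attend week 12 and complete the questionnaires: 24 of 30 = 80%, so domain 9 is met at that visit.
- Of those 24, no scorable goal: 12. GAS completion is 12 / 30 = 40%.
- Domain 10 is unchanged.

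Counting GAS as one questionnaire among the 11 measures in Table 2, with completion pooled, gives (24 × 10 + 12) / (30 × 11) = 252 / 330 = 76.4%, which still passes. Only a separate 75% requirement for each instrument, with GAS included, would catch it. The article does not say that, and GAS has no week-6 assessment.

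**4. What a criterion that can fail would look like.** Suppose domain 9's 75% were applied to week-12 GAS scores among all randomised: 0.75 × 30 = 22.5, so at least 23 of 30. The binomial probability of passing is:

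| True proportion scored | P(at least 23 of 30) |
|---|---|
| 60% | 0.04 |
| 70% | 0.28 |
| 75% | 0.51 |
| 80% | 0.76 |
| 85% | 0.93 |
| 90% | 0.99 |

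A threshold of 80% in each group would be a poor choice. It means 12 of 15, exactly what remains after the planned 20% drop-out. At 80% retention, P(at least 12 of 15) is about 0.65 per group and 0.65 × 0.65 ≈ 0.42 for both, taking the groups as independent.

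**5. Domains 2 and 5.** The ethics review was completed before recruitment. For setting, 60% of 30 is 18. With one recruiting health service the result is 30 of 30 if that service counts as northern Melbourne and 0 of 30 if it does not. No outcome in between is possible under the recruitment as described.

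**The case against.** The strongest reply is that a failure of GAS would not go unseen. Scores are collected at baseline and week 12, effect sizes are calculated for the secondary outcomes, and missing data will be evaluated and reported. Online Resource 2, which is not shown, gives more detail on the measures. A reader might infer that nothing observed in the trial could show GAS to be infeasible. The documents do not support that: the data will be there, and what is missing is a stated criterion that uses them. Nor is the unseen resource likely to supply one, since the article places the deciding criteria in Table 1.

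The reply about domain 9 also stands in part. Poor attendance at week 12 would probably show there, so the gap is confined to participants who attend without a usable score.

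A reader might also infer that the ethics and setting criteria cannot fail. That is not supported either. Approval does not show that the committee raised no concerns, and the article places the recruiting service in Melbourne without saying northern Melbourne, so 0% would fail domain 5. Domain 5 also counts enrolled participants, so it is not independent of trial data.

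Finally, one could put a confidence interval on four interviews. The article gives no interview result and uses the interviews for qualitative feedback, so such an interval would be hypothetical and the point does not rest on one.

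**Conclusion.** The point holds for domain 10. The article sets the trial the task of determining whether GAS is feasible as a primary outcome, and its only primary-outcome criterion neither measures that nor draws on the trial. The size is one named objective without a working test. Randomisation, data collection and effect estimates are unaffected.

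This rests on two readings: that the four interviews described are those meant in Table 1 (no others are described), and that domain 9 does not set a separate requirement for GAS (none is stated).

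The secondary point is smaller. Domain 2 is largely settled before recruitment. The 60% threshold in domain 5 is all-or-nothing and tells the reader little. To say that three of the ten criteria cannot fail would go beyond the documents.

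**What to change.** Before results are seen, add to domain 10 a criterion that the trial's data can fail, for example:
- the proportion of randomised participants with at least one fully scaled goal at baseline;
- the proportion with a week-12 GAS score.

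Report both by group and judge them overall. Set the week-12 threshold in line with domain 9 (75%, at least 23 of 30), or define it among participants who attend, so that it does not merely restate the planned 20% drop-out. The sponsor should choose and justify the baseline threshold. Keep the interviews as supporting evidence for the choice of GAS.

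In Table 1, label domains 2 and 5 as largely determined by design. Replacing domain 5 with a referral-based measure, such as the share of recommended patients who make contact, would need a log of those patients, which the article does not describe.

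The cost is a change of wording in Table 1. The GAS data are already planned, although baseline goals must be counted from the paper sheets because only the change is entered in REDCap. The small downside is that the criterion can now fail: with a true score rate of 80% and a threshold of 23 of 30, the chance of failing is 1 − 0.76 = 0.24.

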### Other variables: limited efficacy testing

In addition to evaluating feasibility, limited efficacy testing will be undertaken on measures to be included in a fully powered randomised trial. These measures are outlined briefly in Table 2 and in specific detail in Online Resources 2.

**Table 2 Tab2:** Other variables measured for limited efficacy testing

Variable	Outcome measure	Timepoints
Goal attainment	Goal Attainment Scaling	Baseline and week 12
Global change	Global Perceived Rating of Change (15-point Likert scale)	Week 6 and week 12
	Patient Global Assessment	Baseline, week 6 and week 12
Foot-specific pain	Foot Health Status Questionnaire—foot pain domain	Baseline, week 6 and week 12
	Manchester-Oxford Foot Questionnaire—foot pain subscale	Baseline, week 6 and week 12
Foot-specific function	Foot Health Status Questionnaire—foot function domain	Baseline, week 6 and week 12
	Manchester-Oxford Foot Questionnaire—walking/standing subscale	Baseline, week 6 and week 12
Disability	Health Assessment Questionnaire—disability index	Baseline, week 6 and week 12
Stiffness	11-point numerical rating scale	Baseline, week 6 and week 12
Fatigue	Functional Assessment of Chronic Illness Therapy-Fatigue (FACIT-Fatigue) version 4	Baseline, week 6 and week 12
Change in physical activity	Global Physical Activity Questionnaire	Baseline, week 6 and week 12

### Procedures

The flow of participants through the trial is displayed in Fig. 1. Potential participants will be initially screened via telephone interview against the inclusion criteria by a research assistant, who will enter data into REDCap. The data collected during this screening telephone interview is outlined in Online Resource 3. During eligibility screening, if the participant is eligible for inclusion an appointment will be made for the baseline assessment with the Chief Investigator. At the baseline appointment, the Chief Investigator will randomise participants to either the intervention or control group after obtaining informed consent to participate in the trial.

**Fig. 1 Fig1:**
[figure not shown]
Diagram of participant flow

The total period of data collection for participants is 12 weeks. Participants who are enrolled in the trial will attend a baseline appointment at La Trobe University Health Sciences Clinic to complete outcome measures and commence podiatry treatment or receive the control intervention depending on their allocation. All outcomes will be completed on a computer and recorded in REDCap except for goals developed for Goal Attainment Scaling, which will be recorded on hard copy sheets for each individual participant. The change in Goal Attainment Scaling (rather than the goal itself) will be recorded by the Chief investigator in REDCap at the week 12 follow-up assessment. At week 6, the research assistant will send outcome measures to participants by email with a link to the REDCap survey. Follow-up assessment at week 12 will be in-person at the La Trobe University Health Sciences Clinic. Participants who are randomised to the intervention group will also attend treatment visits at the La Trobe University Health Sciences Clinic, which will occur depending on the treatment required.

